# Effect of an intraoperative periradicular application of platelet-rich fibrin (PRF) on residual post-surgical neuropathic pain after disc herniation surgery: study protocol for NeuroPRF, a randomized controlled trial

**DOI:** 10.1186/s13063-023-07420-y

**Published:** 2023-06-19

## Abstract

**Background:**

The prevalence of post-surgical lumbar neuropathic radiculopathy is approximately 30%. Poor response to the recommended treatments for neuropathic pain, namely antidepressants and/or gabapentinoids, requires the development of new techniques to prevent chronic pain. One such well-tolerated technique is the administration of autologous plasma enriched in platelets and fibrin (PRF). This approach is largely used in regenerative medicine owing to the anti-inflammatory and analgesic properties of PRF. It could also be an interesting adjuvant to surgery, as it reduces neurogenic inflammation and promotes nerve recovery, thereby reducing the incidence of residual postoperative chronic pain. The aim of the present study is to evaluate the benefit of periradicular intraoperative application of PRF on the residual postsurgical neuropathic pain after disc herniation surgery.

**Methods:**

A randomized, prospective, interventional, controlled, single-blind study with evaluation by a blind outcome assessor will be performed in Strasbourg University Hospital. We will compare a control group undergoing conventional surgery to an experimental group undergoing surgery and periradicular administration of PRF (30 patients in each arm). The primary outcome is the intensity of postoperative neuropathic radicular pain, measured by a visual analog scale (VAS) at 6 months post-surgery. The secondary outcomes are the characteristics of neuropathic pain (NPSI), the quality of life (SF-12 and PGIC), the presence of anxiety/depression symptoms (HAD), and the consumption of analgesics. We will also carry out transcriptomic analysis of a panel of pro- and anti-inflammatory cytokines in blood samples, before surgery and at 6 months follow-up. These gene expression results will be correlated with clinical data, in particular, with the apparition of postoperative neuropathic pain.

**Discussion:**

This study is the first randomized controlled trial to assess the efficacy of PRF in the prevention of neuropathic pain following surgery for herniated disc. This study addresses not only a clinical question but will also provide information on the physiopathological mechanisms of neuropathic pain.

**Trial registration:**

This study is registered at ClinicalTrials.gov: NCT05196503, February 24, 2022.

**Supplementary Information:**

The online version contains supplementary material available at 10.1186/s13063-023-07420-y.

## Background

Neuropathic pain is defined by the International Association for the Study of Pain (IASP) as “pain resulting from an injury or disease affecting the somatosensory system” [1]. From an epidemiological point of view, several large surveys using screening tools have been carried out in different countries. The STOPNEP study carried out in France on more than 30,000 individuals made it possible to estimate the prevalence of chronic pain at approximately 30%, including 7% with neuropathic characteristics, and similar results were yielded in a French 2018 study by Chenaf et al. [2, 3]. In other countries, similar estimates of prevalence (i.e., 6–10%) have been reported [4]. Among the most cited causes is a disc herniation, in almost 1 out of 5 cases [5]. Neuropathic pain remains underdiagnosed in general, with a significant delay in treatment, leading to excessive consumption of opiates and medical nomadism [6]. Thus, the intensity, persistence and impact of chronic pain significantly affect quality of life [7].

Acute lower back pain is one of the most commonly observed acute pains in clinical practice. Its natural history is most often favorable, with healing usually occurring within a few weeks. The problem appears when nerve root pain occurring in the lower back as a result of discoradicular conflict persists. Among these patients, some will benefit from spinal surgery. However, after spinal surgery, some patients will develop residual chronic pain, which has been shown to occur in 10–50% of cases [8]. For approximately 50–70% of these cases, we note the persistence of neuropathic symptomatology [9].

From a pathophysiological point of view, disc compression on the root quickly induces intraneural edema, leading to nerve fiber degeneration complications a few months later [10]. Similarly, intervention with surgical instruments may leave traces, such as inflammatory changes in the dura mater, thus modifying the volume of the thecal sac, or fibrotic scarring at the operating site, which can induce spatial and therefore mechanical stresses. In addition, an alteration of the perineural vascularization, particularly in the vasa nervorum, has been demonstrated in lumbar radiculopathy induced by chronic mechanical compression [11]. This ischemic theory postulates that compression causes venous stasis and/or a decrease in arterial flow within nerve root vascularization, inducing cellular hypoxia and nerve degeneration, thus leading to neuroinflammation phenomena of the nerve roots. Dorsal root ganglion (DRG) cells are involved in the pathophysiological mechanisms of initiation and maintenance of neuropathic pain [12]. Ultimately, the pathophysiology seems to be based on ubiquitous phenomena: a compression or mechanical conflict complicated by ischemic events, followed by degeneration of the nerve fibers, all associated with mechanisms of neuroinflammation [13].

The development of numerous animal models of neuropathic pain has made it possible to clarify some of the pathophysiological mechanisms. Communication between the nervous system and the immune system, in particular via cytokines at the peripheral or central level, contributes to the development and maintenance of neuropathic pain [14]. This neuro-immune balance has been the subject of much research in recent years [15]. Indeed, following a neurological lesion, the activation of immune and glial cells within the nervous tissue, at the site of the injured nerve, the DRG, then the neuraxis, leads to a release of cytokines, initiating and maintaining neuropathic pain [16–18]. Clinical studies have also shown neuropathic pain to induce changes in cytokine expression in nerve structures, such as the nerve and DRG, but also in cerebrospinal fluid [18]. As such, direct or indirect cytokinergic modulation could prove to be an effective therapeutic option against neuropathic pain.

Growth factors such as platelet-derived growth factor (PDGF) have been shown to decrease pro-inflammatory cytokine synthesis [19, 20]. Platelets, in addition to their well-known hemostasis role, contain a large number of growth factors (PDGF, transforming growth factor (TGF-β), etc.) that could play a role in this pro/anti-inflammatory balance [21]. A technique for concentrating growth factors contained in platelets allows to obtain platelet-rich plasma (PRP) by centrifugation of whole blood, then removal of the fraction containing large quantities of blood platelets. PRP injection is an autologous therapeutic tool that has recently emerged. It presents interesting nerve regeneration and analgesic capacities [18].

Other studies go even further by adjusting centrifugation speeds to successfully produce plasma rich in platelets and fibrin (PRF) [22]. Thanks to its fibrin network, PRF has the particularity to solidify within a few minutes after injection. This allows to limit the diffusion space, thereby resulting in an increase in the growth factors local concentration. This technique also allows gradual release (> 1 month) as compared to PRP injection alone [23].

In light of these properties, PRF would be interesting to use in the prevention of neuropathic pain, in particular within the context of spinal surgery. In the current protocol, we have chosen to focus on the prevention of residual neuropathic pain following surgery for herniated disc. Although this study population does not represent the majority of postoperative pain following spinal surgery, a selective population is required in order to assess the effectiveness of PRF in preventing neuropathic pain. To date, this study is the only randomized controlled trial designed to address this question.

## Methods and analysis

### Study design

The present NeuroPRF trial is designed as a superiority, prospective, single-center, randomized, parallel group study, conducted in a single-blind manner, with evaluation by a blind outcome assessor. Eligible patients will be randomized into one of two treatment groups: experimental group (surgery and periradicular administration of PRF) or control group (reference treatment, surgery alone). Patients will be followed for a total of 6 months. This manuscript used the SPIRIT reporting guidelines.

### Involvement in the design of the protocol

Patients and the public were not involved in the design of this study.

### Aim and objectives

The aim of the NeuroPRF trial is to determine whether the intraoperative periradicular application of PRF can prevent residual post-surgical neuropathic pain after disc herniation surgery.

The primary objective is to evaluate the effect of an intraoperative periradicular application of PRF on the intensity of postoperative residual leg neuropathic pain 6 months after primary surgery for a herniated disc.

Secondary objectives evaluate:The incidence and characteristics of residual neuropathic pain;Quality of life;Anxious and depressive symptoms;The correlation between neuropathic pain and gene expression of a panel of cytokines in the blood (specific search for a panel of pro- and anti-inflammatory cytokines);The use of analgesics;Safety.

### Outcomes

Study outcomes are assessed by a designated, blinded study investigator, and the patient (self-assessment), who is also blind to their treatment arm. All outcomes will be assessed at baseline (preoperatively) and at 2 weeks and 6 months after the surgery.

The primary outcome is the intensity of postoperative neuropathic radicular pain, measured by a visual analog scale (VAS). The neuropathic radicular pain will be confirmed by a clinical examination and a “Douleur Neuropathique 4” (DN4) score ≥ 4. Thus, VAS for leg pain will be measured during all follow-up visits: baseline (preoperative), 2 weeks and 6 months postoperative. VAS leg pain will be scored on a 0 to 10 points scale with increments of 1 point (0 being zero pain and 10 being the maximum pain possible).

In order to assess the presence and the neuropathic pain characteristics, the quality of life and the anxiety/depression syndromes, secondary outcomes will be measured at baseline (preoperative), 2 weeks and 6 months postoperative:The incidence and characteristics of residual neuropathic pain, measured by the DN4 and the Neuropathic Pain Symptom Inventory (NPSI) questionnaires, respectively;The evolution of quality of life with the 12-item Short Form Survey (SF-12) and Patients’ Global Impression of Change (PGIC) questionnaires;Anxiety and depressive symptoms with the Hospital Anxiety and Depression (HAD) questionnaire;The level of gene expression of a panel of pro- and anti-inflammatory cytokines in the blood (Table 1) using multiplex quantitative PCR;The use of analgesics;Incidence of adverse events (AE) and serious adverse events (SAE).

**Table 1 Tab1:** Panel of genes used for gene expression analysis

**Pro-inflammatory cytokines**	TNF-α, IL-1β, IL-6, IL-8, IL-17, IL-18, MCP-1, RANTES, CXCL2, fractalkine
**Anti-inflammatory cytokines**	IL-2, IL-4, IL-10, IL-1RA
**Signal transduction proteins**	IκB, NFκB p65 subunit

*TNF* tumor necrosis factor, *IL* interleukin, *MCP* monocyte chemoattractant protein, *RANTES* regulated on activation normal T cell expressed and secreted, *CXCL2* chemokine (C-X-C motif) ligand 2, *IL-1RA* interleukin 1 receptor antagonist, *NFκB* nuclear factor kappa B, *IκB* inhibitor of nuclear factor kappa B

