### Statistical analysis

The analyses will be carried out using Bayesian methods.

Firstly, a descriptive analysis will be carried out. For the categorical variables, the frequency of each value and the cumulative frequency will be given. For the quantitative variables, location parameters (mean, median, minimum, maximum, first and third quartiles) and dispersion parameters (standard deviation, variance, range and interquartile range) will be given. The parameters will be estimated firstly on raw data, and secondly within the Bayesian paradigm, on the posterior distribution, for each variable.

Secondly, to compare the difference of the means of the VAS, a Bayesian linear regression will be performed. The regression will be simple linear or generalized depending on the distribution of the data. To meet the secondary objectives, Bayesian linear regressions will be performed for continuous variables, and Bayesian logistic regressions for categorical variables.

The regressions will be firstly carried out without adjustment and secondly with an adjustment on sex and age. Subgroup analyses are not planned.

The priors will be on the one hand very uninformative and on the other hand informative in the context of a sensitivity analysis.

For each analysis, the posterior distribution of the parameter of interest (rate, proportion, mean, odds ratio, regression coefficient, etc.) will be estimated using Markov chain Monte Carlo (MCMC) draws. The default number of iteration is 200,000 with a burning of 10,000 and a thinning of 2. Algorithm convergence will be assessed graphically and with the Gelman and Rubin’s convergence diagnostic. Autocorrelation will be assessed graphically and, if required, the number of iterations and thinning will be increased to reduce as much as possible the autocorrelation.

Credibility intervals will be calculated at 95% using the quantile method. A particular factor will be considered to exert an effect on the variable in question if the probability that the effect is greater than the reference value is greater than 0.975 or less than 0.025.

The proportion of missing data will be given for each variable. Missing data will be treated by simple deletion of cases if these values are very few or by multiple imputation in the opposite case.

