## Discussion

The platelet-rich plasma was historically used in dentistry for its osteo-regenerative properties. This technique has been rapidly extended to other fields, such as rheumatology or sports medicine. In the field of pain, some studies have reported its analgesic properties on neuropathic pain of peripheral origin, while perineural injection of PRP has been shown to improve pain in patients with various etiologies, such as postherpetic neuralgia, chronic post-surgical pain, or traumatic peripheral nerve injury [30–32].

Furthermore, it could be an interesting adjuvant to surgery. In a case report, the use of intraoperative PRP during nerve decompression surgery following digital trauma was shown to significantly reduce neuropathic pain and improve functional recovery [33]. PRP could also be of interest for neurosensory recovery [34]. Following the example of these clinical studies, intraoperative PRP could act to reduce neurogenic inflammation, promote nerve healing, and thus reduce the incidence of residual postoperative chronic pain.

We elaborated the first randomized controlled trial to assess the efficacy of PRF in the prevention of neuropathic pain following surgery for herniated disc. This study not only addresses a clinical question but will also provide information on the physiopathological mechanisms of neuropathic pain. However, this trial has some limitations. This study is limited by its single-center design. The selected study population (participants undergoing spinal surgery for a herniated disc) can be considered a limitation in that this population does not represent the majority of patients who experience chronic pain following spinal surgery.

Thus, the interest of this therapy is that PRF could also be an interesting adjuvant to surgery and may thus block the initiation of neuropathic pain mechanisms [18].

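### The DN4 'incidence' outcome is a postoperative status that mixes persistent with new neuropathic pain, and its planned regression omits the baseline DN4 the trial already collects

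*Protocol article*

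**What the plan says.** The aim (Aim and objectives) is to "determine whether the intraoperative periradicular application of PRF can prevent residual post-surgical neuropathic pain after disc herniation surgery". The primary objective concerns the effect "on the intensity of postoperative residual leg neuropathic pain 6 months after primary surgery for a herniated disc", measured by VAS. The outcome at issue here is secondary (Outcomes): "The incidence and characteristics of residual neuropathic pain, measured by the DN4 and the Neuropathic Pain Symptom Inventory (NPSI) questionnaires, respectively". The threshold appears in the same section, under the primary outcome: "The neuropathic radicular pain will be confirmed by a clinical examination and a “Douleur Neuropathique 4” (DN4) score ≥ 4".

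Eligibility (Setting and patient recruitment) requires radiculopathy from a lumbar disc herniation with surgery scheduled. It neither requires nor excludes a DN4 of 4 or more. The DN4 is completed by the examining clinician before surgery, at 2 weeks and at 6 months (Description of clinical examination and questionnaires).

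Categorical secondary outcomes go into Bayesian logistic regression, and the Statistical analysis section fixes the covariates: "The regressions will be firstly carried out without adjustment and secondly with an adjustment on sex and age. Subgroup analyses are not planned". Randomisation has no stratification factors (Timeline and description of processes).

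The article's vocabulary varies. The Background says of chronic pain after spinal surgery that "we note the persistence of neuropathic symptomatology". The Abstract plans to correlate gene expression with the *apparition* of postoperative neuropathic pain. The Discussion says PRF "may thus block the initiation of neuropathic pain mechanisms".

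**The concern.** Incidence means new cases among people who were free of the condition. Residual means what is left over. The outcome's name uses both words, and the article gives no rule to choose between them. Every participant enters with a compressed, painful nerve root, and the Background attributes nerve-fibre degeneration and neuroinflammation to that compression, so preoperative DN4 ≥ 4 is to be expected in some patients. As written, a patient positive before and after surgery counts in the same way as one who turns positive after it.

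Two things follow. First, an effect on this outcome could be faster resolution, blocked onset or both, and the pooled count cannot say which. This also affects the gene-expression analysis if it uses the same status as a marker of onset. Second, baseline DN4 is likely to be a strong predictor of 6-month DN4, yet it has no stated place in the between-arm model. In a trial of 30 per arm without stratification, that gives up some efficiency and leaves chance imbalance in this factor uncorrected.

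**Working it through.** **1. The plan's own figure.** The only calculated figure is the power for the VAS: 25 per group, difference 1, SD 1, two-sided 5%. The noncentral t with 48 degrees of freedom gives 93.4%, against the stated 93.5%. It reproduces and is not in dispute. No figure is given for the DN4 outcome.

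**2. Anchor.** The Abstract puts post-surgical neuropathic radiculopathy at about 30%. The Background's ranges imply 0.10 × 0.50 = 5% to 0.50 × 0.70 = 35%. I use 30% as the 6-month DN4-positive rate. This is an assumption towards the upper end of that range. I also assume that the regression uses the 6-month visit, which the article does not say for this outcome.

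**3. Make-up of the positives.** Let p be the preoperative DN4-positive share, and r1 and r0 the 6-month risks in baseline-positive and baseline-negative patients. None of these is in the documents. They are chosen so that p·r1 + (1 − p)·r0 = 0.30.

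| p | r1 | r0 | Persistent, p·r1 | New, (1 − p)·r0 | Persistent share | New cases per 30 controls |
|---|---|---|---|---|---|---|
| 0.30 | 0.60 | 0.171 | 0.18 | 0.12 | 60% | 3.6 |
| 0.50 | 0.50 | 0.10 | 0.25 | 0.05 | 83% | 1.5 |
| 0.70 | 0.40 | 0.067 | 0.28 | 0.02 | 93% | 0.6 |

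A wider range (p from 0.30 to 0.90, r0 from 0.05 to 0.15) puts the persistent share between 1 − 0.7 × 0.15/0.30 = 65% and 1 − 0.1 × 0.05/0.30 = 98%.

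**4. Chance imbalance.** With two independent Binomial(30, p) counts, the probability of a difference of 6 or more patients (20 points) is 12.0%, 15.5% and 12.0% for p = 0.30, 0.50 and 0.70. A 20-point imbalance shifts the compared rate by 0.20 × (r1 − r0) = 8.6, 8.0 and 6.7 points. The standard error of the unadjusted difference is √(2 × 0.30 × 0.70/30) = 11.8 points, so each shift is below one standard error.

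**5. Gain from using baseline DN4.** On the risk-difference scale, comparing within baseline strata replaces 0.30 × 0.70 = 0.21 by p·r1(1 − r1) + (1 − p)·r0(1 − r0).
- p = 0.30: 0.171, standard error √(2 × 0.171/30) = 10.7 points
- p = 0.50: 0.170, standard error 10.6 points
- p = 0.70: 0.187, standard error 11.2 points

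Against 11.8 points, this is a reduction of roughly 6% to 10%: useful but modest.

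**6. What the sample can infer.** For two proportions, power = Φ[(d − 1.96·se0)/se1], with se0 from the pooled rate. Halving the pooled rate from 30% to 15% with 25 evaluable per arm gives Φ[(0.15 − 1.96 × 0.118)/0.116] = Φ(−0.70) = 24%. With 30 per arm it is 28%, and 80% power needs 121 per arm. For new onset alone, over the wider range in step 3, there are 25 × (1 − p) = 2.5 to 17.5 baseline-negative patients per arm, 0.1 to 2.6 expected new control cases, and about 4% to 10% power to detect a halving.

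**The case against.** A reader might go further and infer that the trial cannot support its aim of prevention at all. The documents do not bear that out. The aim is to prevent residual pain, and the Background describes that condition as persistence, so counting patients who remain positive fits the aim. Randomisation balances preoperative DN4 in expectation, so the arm comparison is unbiased. Chance imbalance is ordinary sampling variation and is already reflected in the credible interval. The aim also rests mainly on the VAS, not on this outcome. Blocking initiation is a hedged Discussion remark that no planned analysis tests. All of this stands.

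It can also be said that the counting rule is inferred. The article does not state that persistent and new cases are pooled, a condensed article may leave the case definition to the full protocol, and ruling out subgroup analyses does not forbid a table of DN4 by visit. This stands in part. The split could still be tabulated, but the covariate set is not left open: the article states it, and baseline DN4 is not in it.

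Finally, every share and risk in steps 3 to 5 is assumed. That is correct. They show what is possible, not what will happen, and they do not establish that the outcome would mainly measure non-resolution.

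**Conclusion.** The point holds in a limited form. The outcome labelled as incidence is, as written, a postoperative DN4 status in patients who may already be positive at entry. The arm comparison is valid for preventing residual pain, but it cannot distinguish blocked onset from resolution. It therefore gives no basis for onset wording, including the *apparition* language attached to the gene-expression correlation.

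Leaving out baseline DN4 does not bias the comparison. It costs some efficiency and some protection against chance imbalance: on the illustrative assumptions, a standard error about 6% to 10% larger than necessary, and a possible shift of 7 to 9 points with a 20-point imbalance. The true size depends on the preoperative DN4-positive share and on how strongly it predicts 6-month status, neither of which the documents give. The change is worth making because it is nearly free, not because the trial is unsound without it.

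**What to change.** - **Statistical analysis:** add baseline DN4 status (≥ 4 or < 4), or the baseline score, to the adjusted logistic regression of DN4 ≥ 4 at 6 months, beside sex and age. Keep the unadjusted analysis.
- **Aim and objectives, Outcomes:** call the outcome the proportion with DN4 ≥ 4 at 6 months.
- **Reporting:** tabulate by arm the new-onset cases (below 4 before surgery, 4 or more at 6 months) and the persistent cases (4 or more at both). Keep this descriptive, because onset events will be too few for inference.
- **Wording:** describe an effect on the pooled outcome as less residual neuropathic pain, persistent or new. Do not present it, or the gene-expression correlation in the Abstract, as prevention of onset.

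No new data, visits or patients are needed. The cost is one more model term with few events: at 30% in both arms, 0.30 × 60 = 18 in all. If almost no baseline-negative patient turns positive, the coefficient for binary status will be poorly determined under the very uninformative prior. Using the score eases this. The adjusted odds ratio is also conditional on baseline DN4, so it should not be read as the same quantity as the unadjusted one.
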